## Statistical analysis plan, including sample size and power calculations

### Birthweight centiles

In a previous study, the mean (SD) birth weight in a cohort of obese women (mean BMI 34 kg/m^2^) was 4.0 (0.6) kg.^36^ We hypothesise that metformin will reduce mean birth weight by 0.2 kg, corresponding to a reduction in birthweight centile of 0.33 SD. We believe that this reduction is clinically relevant, but is a relatively conservative estimate of likely reduction in birthweight centile induced by metformin, given that mean birth weight in the study described above in a parallel non-obese cohort was 3.4 kg. A sample size of 143 in each group will have 80% power to detect a difference in mean birthweight centile of 0.33 SD (the difference between a placebo mean of 4.0 kg and a metformin mean of 3.8 kg) at the 5% significance level (2-sided) using a two group t test; a sample size of 163 in each group will give the study 85% power to detect these differences. In practice, we will recruit a larger sample size to allow loss to follow-up.

### Type of analysis and statistical tests

The primary analysis will be by intention to treat. Mean birthweight centile will be compared between the two groups using a two-sample t test, but with the analysis stratified for the same factors as the randomisation. Correlations within the metformin and placebo groups will be used to determine associations between insulin resistance and adverse pregnancy outcomes.

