**Methods and analysis:**

The Efficacy of Metformin in Pregnant Obese Women, a Randomised controlled (EMPOWaR) trial is a double-masked randomised placebo-controlled trial to determine whether metformin given to obese (body mass index >30 kg/m^2^) pregnant women from 16 weeks’ gestation until delivery reduces the incidence of high birthweight babies. A secondary aim is to test the mechanism(s) of any effect. Obese women with a singleton pregnancy and normal glucose tolerance will be recruited prior to 16 weeks’ gestation and prescribed study medication, metformin or placebo, to be taken until delivery. Further study visits will occur at 28 and 36 weeks’ gestation for glucose tolerance testing and to record anthropometric measurements. Birth weight and other measurements will be recorded at time of delivery. Anthropometry of mother and baby will be performed at 3 months postdelivery. As of January 2014, 449 women had been randomised across the UK.

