## Objectives

### Primary objective

To determine the efficacy of metformin (up to 2500 mg daily), given to obese pregnant women from between 12 and 16 weeks’ gestation until delivery, in reducing gestational age-adjusted and sex-adjusted birthweight centile of the baby.

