## Design

The design is a double-masked randomised placebo-controlled trial, with embedded substudies to explore mechanism of action of metformin, in a population of ∼400 obese pregnant women (figure 1).

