## Outcomes

### Primary outcome

Z-score corresponding to the gestational age-adjusted and sex-adjusted birthweight centiles of the baby.

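### The primary outcome is a birthweight z-score, but the stated primary analysis is a t test of mean birthweight centile; the analysis sentence should name the z-score, and 0.2 kg should be given only as an approximate translation of the target

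*Protocol article*

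**What the plan says.** All references are to the Protocol article.

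- **Primary outcome:** the analysed variable is the "Z-score corresponding to the gestational age-adjusted and sex-adjusted birthweight centiles of the baby".
- **Primary objective:** the aim is expressed on the centile, "in reducing gestational age-adjusted and sex-adjusted birthweight centile of the baby".
- **Type of analysis and statistical tests:** "Mean birthweight centile will be compared between the two groups using a two-sample t test". This comparison is to take account of centre and BMI group, since both were used to stratify allocation. The article describes the primary comparison nowhere else.
- **Birthweight centiles (sample size):** the source figure is that "the mean (SD) birth weight in a cohort of obese women (mean BMI 34 kg/m^2^) was 4.0 (0.6) kg". A fall of 0.2 kg is then described as "corresponding to a reduction in birthweight centile of 0.33 SD". On that basis, 143 per group gives 80% power and 163 per group gives 85%, two-sided 5%, by a two-group t test. The section adds that more women will be recruited to allow for loss to follow-up.

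**The concern.** One primary endpoint carries two variable names. The outcome section fixes a z-score and the analysis section compares mean centiles. These are not interchangeable: the centile is 100·Φ(z), bounded at 0 and 100 and compressed towards the upper end, where babies of obese mothers are expected to lie. The same shift in z gives a different number of centile points depending on where the placebo group sits, and the mean of the centiles is not the centile of the mean z. An analyst could use either scale and cite the protocol for it, and pre-specification is meant to remove that choice.

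A second, lesser question of labelling sits in the sample-size section. The 0.33 SD is 0.2 kg divided by 0.6 kg. The document describes 0.6 kg as the SD of birth weight and states no adjustment, while the outcome is adjusted for gestational age and sex. The clinical relevance claimed for the target is attached to 0.2 kg, so the translation between the two matters for interpretation.

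**Working it through.** **1. The plan's own figures.** Inputs from the sample-size section: difference 0.2 kg, SD 0.6 kg, two-sided 5%, two-group t test. Standardised difference d = 0.2/0.6 = 0.333. The exact (noncentral t) calculation gives 142.2, so 143 per group for 80% power, and 162.6, so 163 per group for 85%. Power is 80.2% at 143 and 85.1% at 163. Both stated sizes reproduce. They hold for any normally distributed outcome with a true difference of 1/3 of its SD, and so for a t test on z-scores.

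**2. The analysis sentence taken literally.** Assumptions, not in the document: z is normal with SD 1, the placebo mean z is 0, 0.5 or 1.0, and metformin lowers z by 1/3. Centile = 100·Φ(z). The mean and SD of the centile in each arm come from numerical integration, and d on the centile scale is the difference in means over the pooled SD.

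| Placebo mean z | Mean centile, placebo / metformin | Difference | Pooled SD | d | Power, 143 per arm | Power, 163 per arm | Power, 191 per arm | n per arm for 80% |
|---|---|---|---|---|---|---|---|---|
| 0 | 50.0 / 40.7 | 9.3 | 28.5 | 0.326 | 78.5% | 83.6% | 88.9% | 149 |
| 0.5 | 63.8 / 54.7 | 9.1 | 28.1 | 0.325 | 78.2% | 83.3% | 88.6% | 150 |
| 1.0 | 76.0 / 68.1 | 7.9 | 25.0 | 0.315 | 75.7% | 81.0% | 86.7% | 159 |
| z-score test, any mean | – | 1/3 z | 1 | 0.333 | 80.2% | 85.1% | 90.1% | 143 |

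The 191 per arm is 449 × 0.85 / 2 = 190.8. The 449 is the number randomised by January 2014 in the abstract; the 15% loss is an assumption.

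Two things follow. The same shift in z is 9.3 centile points in one setting and 7.9 in another, so the scale determines what is estimated. The cost in power is about 2 to 5 percentage points at 143 per arm and about 1 to 3 at 191.

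**3. The translation of 0.33 SD into 0.2 kg.** This is exact only if the SD of birth weight after adjustment for gestation and sex is also 0.6 kg, which the document does not show. Taking adjusted SDs of 0.45, 0.50 and 0.55 kg (assumptions):

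| Adjusted SD | 0.2 kg as d | Power for 0.2 kg, 143 per arm | d = 1/3 in kg |
|---|---|---|---|
| 0.45 kg | 0.2/0.45 = 0.444 | 96.3% | 0.45/3 = 0.15 |
| 0.50 kg | 0.2/0.50 = 0.400 | 92.1% | 0.50/3 = 0.17 |
| 0.55 kg | 0.2/0.55 = 0.364 | 86.5% | 0.55/3 = 0.18 |
| 0.60 kg (as stated) | 0.333 | 80.2% | 0.20 |

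With a smaller adjusted SD, the planned size has more than the stated power for a 0.2 kg effect.

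**The case against.** The best defence is that this is shorthand. The outcome section is explicit, a centile expressed in SD units reads most naturally as a z-score, and a two-sample t test suits a z-score. That reading is plausible, and it means the fault may be one of wording only. It does not remove the point: nothing in the article says that centile stands for its z-score, and the sentence that specifies the primary analysis names the other variable.

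Three stronger readings are tempting, and the document does not support them.

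- **That the test and target do not fit the outcome, so the sample size is wrong.** The stated 143 and 163 are correct for a z-score t test at d = 1/3. Even the literal centile test exceeds 80% power at 163 per arm in every case tabulated above.
- **That the stated powers refer to the wrong number of women.** The powers are for 2 × 143 = 286 or 2 × 163 = 326 women, whereas the Design section gives about 400 and the abstract reports "449 women had been randomised across the UK". The sample-size section explains the gap as an allowance for loss to follow-up: 326 analysed out of 400 leaves room for 74/400 = 18.5% loss. This is ordinary inflation and not an error.
- **That the kilogram conversion leaves the trial short of power.** A smaller adjusted SD works in the safe direction. It is also only an inference that the 0.6 kg is unadjusted, because the document calls it simply the SD of birth weight. No section plans to report the result through this conversion, and birth weight is recorded, so a difference in kilograms can be estimated directly.

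The placebo mean z of 1.0 in the working should be read with the same caution. It is close to (4.0 − 3.4)/0.6 from the protocol's two cohorts, but that uses the same kilogram SD and treats the non-obese mean as z = 0, which the document does not say. It is an assumed upper case.

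**Conclusion.** The mismatch between outcome and analysis is real and should be corrected; its consequences are limited. The declared primary outcome is a z-score, and the stated primary analysis compares a different variable with a different effect estimate. If the sentence were followed literally, power would be about 76 to 79% instead of 80% at 143 per arm, and about 87 to 89% instead of 90% at 191 per arm. This assumes a 1/3 SD shift, SD of z equal to 1, placebo mean z between 0 and 1 and, for the 191, a 15% loss.

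Equating 0.33 SD with 0.2 kg is unsupported for an adjusted outcome, but this is a matter of labelling. With an adjusted SD of 0.45 to 0.55 kg (assumption), 0.33 SD would be about 0.15 to 0.18 kg and the planned size conservative. Power would fall below that stated for 0.2 kg only if the adjusted SD among the trial's babies exceeded 0.6 kg, and nothing in the document suggests that. Severity: minor to moderate.

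**What to change.** 1. **Type of analysis and statistical tests:** name the mean birthweight z-score as the quantity compared, in place of the mean centile. Keep the intention-to-treat basis and the stratification by the randomisation factors. Back-transform to centiles for presentation only.
2. **Birthweight centiles (sample size):** state the target as a z-score difference of 0.33 SD, with the SD of z assumed. Give 0.2 kg as an approximate translation only, noting that the 0.6 kg is the SD of birth weight and not of the adjusted measure. The 143 and 163 per group can stay, with d given as 0.2/0.6 = 0.333.

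The cost is a few words in two sections. Data collection, randomisation and recruitment are unaffected. The change should be made before unmasking, so that the choice of scale is on record before any result is seen.

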## Background, including rationale and any previous systematic reviews

Rates of obesity, as defined by a body mass index (BMI) greater than 30 kg/m^2^, are rising alarmingly in the UK and throughout the world. Around 27% of adults in Scotland are now obese and 32% of Scottish children have a weight outwith a healthy range for their age.^1^ Obesity rates in England^2^ and the USA^3^ are similar. The increase in average BMI during pregnancy over the past 20 years has been well documented.^4^ Rates of maternal obesity in women booking for antenatal care in the UK are now around 20%. There has also been a substantial increase in mean birth weight and in the incidence of being born large for gestational age over the past few decades.^5^ The secular rise in maternal weight at delivery appears to be the factor most strongly correlated with the increase in birth weight.^5^
^6^ Positive correlations have also been shown between birth weight and both maternal pregravid weight^7–9^ and weight gain in pregnancy,^10^ with odds of high birth weight some 2.4 times greater in morbidly obese compared with lean women.^11^

This increase in mean birth weight is of concern because it is linked to an increased likelihood of child and adult obesity. A systematic review showed a positive correlation between birth weight and obesity during adulthood.^12^ The association between high birth weight and later life obesity is also supported by two large epidemiological studies^13^
^14^ both of which found obesity to be a long-term correlate of high birth weight. A subsequent prospective study found that children who were large for gestational age at birth and exposed to an intrauterine environment of maternal obesity are also at increased risk of developing metabolic syndrome.^15^ Our own recent work suggests that offspring of obese pregnant women are at increased risk of premature death in adulthood.^16^ Thus, the increase in rates of maternal obesity are setting up a vicious cycle, leading to increased birth weight and increased rates of child and adult obesity, contributing to an epidemic of obesity which has become one of the most significant contributors to global ill health.

Women who are obese during pregnancy are also themselves at greater risk of a number of adverse outcomes, including gestational diabetes,^17^ pre-eclampsia^18^ and stillbirth.^19^

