Considerable evidence implicates insulin resistance or hyperglycaemia as the mechanism by which maternal obesity causes excessive neonatal birth weight. While modest insulin resistance is physiological in pregnancy and generates maternal glucose, free fatty acids and amino acids as substrates for fetal growth, obese pregnant women are more insulin resistant than their lean counterparts^6^ leading to a further amplification of nutrient availability with consequent excessive fetal growth. There is a strong correlation between insulin resistance in late gestation and both birth weight and fat-free mass at birth.^26^ The Hyperglycaemia and Adverse Pregnancy Outcomes (HAPO) trial^27^ confirms that there is a linear relationship between hyperglycaemia and birth weight, even at glucose levels not usually considered abnormal during pregnancy. The Australian Carbohydrate Intolerance Study in Pregnant Women (ACHOIS)^28^ confirms that treating hyperglycaemia can substantially reduce both the incidence of large for gestational age babies and other perinatal complications. Thus, metformin, by reducing insulin resistance, could have a major impact in reducing excess birth weight in obese pregnant women.

This study is timely because of emerging evidence about the safety and efficacy of metformin. It is a licensed first-line therapy for the treatment of type 2 diabetes and is endorsed by National Institute for Health and Care Excellence (NICE) as a treatment for gestational diabetes.^29^

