## Centre(s)

Seventeen hospitals in the UK.

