## Inclusion and exclusion criteria

### Screening phase inclusion criteria

Caucasian obese (BMI ≥30 kg/m^2^) pregnant women between 12^+0^ and 16^+0^ weeks’ gestation;Age greater than or equal to 16 years;Signed informed consent form.

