## Randomisation

Eligible participants will be randomly assigned to active treatment with metformin or an identical looking placebo. This will be documented in the patient's paper case record and/or computer file to show the woman's participation in the trial.

Participants will be randomised via a web portal connected to a central randomisation facility based at the trial data centre, the Edinburgh Clinical Trials Unit, University of Edinburgh. Baseline eligibility data will be required before randomisation. Participants will be randomised in a 1:1 ratio to metformin or placebo. Randomisation will be stratified by treatment centre and BMI 30–39 vs >40 kg/m^2^.

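### The primary analysis uses baseline BMI only as a two-level band and baseline glucose not at all; a prespecified regression on both would gain some precision at no cost, and the BMI bands should be written without a gap

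*Protocol article*

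**What the plan says.** The primary outcome is the "Z-score corresponding to the gestational age-adjusted and sex-adjusted birthweight centiles of the baby". Under *Type of analysis and statistical tests*, the intention-to-treat comparison of means is made "using a two-sample t test, but with the analysis stratified for the same factors as the randomisation". Under *Randomisation*, those factors are given: allocation is "stratified by treatment centre and BMI 30–39 vs >40" kg/m². No other covariate is named for the primary comparison.

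Three other parts of the article bear on this:

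- *Centre(s)* lists "Seventeen hospitals in the UK". *Screening phase inclusion criteria* admits "Caucasian obese (BMI ≥30 kg/m^2^) pregnant women", with no upper limit on BMI.
- *Background* says: "Positive correlations have also been shown between birth weight and both maternal pregravid weight" and weight gain in pregnancy. It also reports, from a large cohort, that "there is a linear relationship between hyperglycaemia and birth weight, even at glucose levels not usually considered abnormal during pregnancy".
- *Methods* and Table 3 show height, weight and a 75 g oral glucose tolerance test (baseline and 2-hour samples) taken at the consent visit, before randomisation. The glucose test decides eligibility, so missing values should be rare.

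**The concern.** The protocol's own rationale says that maternal weight and glucose go with birth weight. Both are in hand for every randomised woman before allocation. The primary analysis nevertheless reduces BMI to two levels and leaves glucose out. When a baseline variable explains part of the outcome variance, leaving it out makes the confidence interval for the treatment effect wider than it need be. What is at stake is precision, not validity.

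There is also a smaller point of wording. The bands 30–39 and >40 do not meet. Read literally, a BMI above 39 and up to and including 40 has no band. If 30–39 is taken as whole numbers (30 to 39.9), a BMI of exactly 40 still has none. Because the analysis uses the same factors as the randomisation, the gap carries over into the analysis text.

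**Working it through.** **Inputs from the document** (*Birthweight centiles*): difference 0.2 kg, SD 0.6 kg, two-sided 5%, two-group t test, 1:1 allocation; 143 per group for 80% power and 163 for 85%.

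**Step 1: reproduce the plan.** The standardised difference is d = 0.2/0.6 = 1/3. The noncentral t calculation gives 142.2 per group for 80% and 162.6 for 85%, which round up to 143 and 163. The stated figures reproduce exactly. They rest on the unadjusted SD, so they take no credit for covariates.

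**Step 2: effect of adjustment.** If baseline covariates explain a share R² of the outcome variance, the residual SD is the original SD × √(1 − R²). The effective difference is then d = (1/3)/√(1 − R²), and the sample is worth 1/(1 − R²) times as many women. The document gives no R², so 1 to 15% is an **assumption**. The sizes of 200 and 224 per arm follow from the roughly 400 women under *Design* and the 449 randomised by January 2014 in the Abstract (449/2 ≈ 224), with no losses taken off.

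| Assumed R² | 1/(1 − R²) | Power, 143/arm | Power, 163/arm | Power, 200/arm | Power, 224/arm |
|---|---|---|---|---|---|
| 0 (no adjustment) | 1.000 | 80.2% | 85.1% | 91.4% | 94.1% |
| 1% | 1.010 | 80.6% | 85.4% | 91.7% | 94.3% |
| 5% | 1.053 | 82.2% | 86.8% | 92.7% | 95.1% |
| 10% | 1.111 | 84.2% | 88.5% | 93.9% | 96.0% |
| 15% | 1.176 | 86.1% | 90.2% | 95.0% | 96.8% |

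The few degrees of freedom spent on covariates are ignored.

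**Step 3: allow for the band already in the analysis.** The table compares adjustment with none, but the stated analysis already includes the BMI band. For illustration, assume a skewed BMI distribution starting at 30 (30 plus a gamma variable with shape 2 and scale 3.75), which puts about 25% of women at 40 or above. The band then holds about 64% of the BMI variance. If BMI correlates with the outcome at r, the band accounts for 0.64r² and continuous BMI for r². At 143 per arm:

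- r = 0.1: 80.5% with the band, 80.6% with continuous BMI (gain 0.1 points).
- r = 0.3: 82.5% with the band, 83.8% with continuous BMI (gain 1.3 points).

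Replacing the band with continuous BMI therefore adds little on its own. Any larger gain would have to come from glucose, which the stated analysis does not use.

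**Step 4: the bands.** Eligibility runs from 30 upward without limit. Set against 30–39 and >40, the value 40.0 falls in neither band on any reading, and values above 39 and below 40 fall in neither on the literal one.

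**The case against.** The strongest objection is that this is a preference. A randomised comparison stratified on its randomisation factors is valid without further covariates, the sample size does not rely on them, and covariate lists are commonly left to the statistical analysis plan, which is not shown. The first two parts stand, and they are why nothing here is called an error. The third has less force: the article does fix a primary method, and a better use of data already being collected can be proposed against it.

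The size of the gain is also open to challenge, fairly. The cited evidence concerns pregravid weight and another cohort's glucose values. This trial takes only women with BMI of at least 30 and excludes gestational diabetes at screening, so both predictors have a restricted range and R² within the trial may be low. At the numbers actually being recruited, power is already above 90% before losses.

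A reader might draw four stronger conclusions, which the document does not support:

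- **That baseline BMI is discarded.** It is used, as a band; only the information within bands is lost.
- **That a stratified t test is no valid analysis.** The name is loose, and 17 centres by 2 bands make up to 34 strata. But the authors qualify the simple test themselves, and the ordinary reading is a comparison of means adjusted for the strata.
- **That women near BMI 40 could not be properly randomised.** Allocation runs through a central web portal that requires baseline data, and 449 women had been randomised. The system must have placed each one. The gap is in the text.
- **That maternal height should be a separate covariate on the protocol's own evidence.** The article does not say that height predicts birth weight.

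**Conclusion.** The point holds as an improvement in efficiency together with a wording correction. There is no bias, and the stated power is met without the change. On an assumed R² of 1 to 15%, and against no adjustment, the gain is 0.4 to 5.9 points of power at 143 per arm and about 0.3 to 3.6 points at 200 per arm; at 224 per arm it is at most 2.7 points. Against the analysis as stated, which already includes the band, it is smaller still. These figures depend wholly on the assumed R² and take the planning difference of one third of an SD as true. The gap in the bands is certain on the text for a BMI of exactly 40, but nothing shows that it affected allocation.

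**What to change.** 1. Name the primary analysis as a linear regression of the birthweight z-score on treatment, centre, continuous baseline BMI, and baseline fasting and 2 h glucose, by intention to treat.
2. Keep the model with treatment and the stratification factors only (centre and BMI band) as a sensitivity analysis.
3. Fix both in writing before unmasking. *Concealment of allocation* keeps the masking in place until the database is locked, so this can be done without knowledge of results.
4. Restate the BMI bands under *Randomisation* so that every eligible value has one band, matching what the portal applied, and use the same definition in the sensitivity analysis.

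The cost is a few sentences and a few lines of code. No further data or participants are needed, and the sample size calculation can stay as it is.

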### Secondary objectives

To determine the pattern of association between insulin resistance and adverse pregnancy outcomes, including incidence of pregnancy-induced hypertension, pre-eclampsia, caesarean section, postpartum haemorrhage, maternal weight gain during pregnancy and incidence of the baby's admission to the neonatal unit.To determine the effect of metformin on maternal body composition.To determine the effect of metformin on neonatal body composition.To determine the effect of metformin on maternal inflammatory and metabolic variables (measured at 28 and 36 weeks’ gestation) and on neonatal inflammatory variables (measured in cord blood at birth).To confirm that metformin does not increase the rate of babies with a low birthweight centile.To determine the efficacy (as opposed to the effectiveness) of metformin when analysis is restricted to those with pharmacological circulating levels of drug.A series of nested substudies will also be performed with the following objectives:
To determine the effect of metformin on maternal cortisol levels in obese pregnant women.To determine the effect of metformin in hepatic and peripheral insulin sensitivity at 36 weeks’ gestation in obese pregnant women.To determine the effect of metformin on endothelium-dependent flow-mediated dilatation in obese pregnant women.To determine the effect of metformin on maternal subcutaneous and visceral adipose tissue deposition and hepatic and skeletal muscle ectopic fat deposition during pregnancy.To determine the effect of metformin on fetal liver volume and subcutaneous fat deposition.To determine the effect of metformin on myometrial contractility and myometrial glycogen storage in obese pregnant women.To determine the effect of metformin on placental glucocorticoid receptor and 11 βHSD 1 and 2 mRNA levels.

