### Secondary outcomes

Maternal insulin resistance at 36 weeks’ gestation, which will be correlated with adverse pregnancy outcomes.Maternal anthropometry and body composition at 16 and 36 weeks’ gestation and 3 months postpartum.Baby anthropometry and body composition at birth and 3 months of age.Maternal inflammatory markers, lipid and fatty acid indices prior to starting treatment and again at 28 and 36 weeks’ gestation including CRP, IL-6, leptin, lipid profile, non-esterified fatty acids, polyunsaturated fatty acids and PAI1/PAI2 ratio.Neonatal CRP, glucose, insulin and other inflammatory and metabolic indices as previously described (measured in cord blood at birth).Incidence of low birthweight centile.Gas chromatography mass spectrometry measurement of metformin in maternal plasma to determine adherence.Secondary outcomes from nested substudies;
Maternal salivary cortisol levels at baseline, 28 and 36 weeks’ gestation.Hepatic and peripheral insulin sensitivity at 36 weeks’ gestation as measured by the hyperinsulinaemic euglycaemic clamp technique.Maternal brachial artery endothelium flow-mediated dilatation measured at 16 and 36 weeks’ gestation.Maternal subcutaneous and visceral adipose tissue deposition and hepatic and skeletal muscle ectopic fat deposition assessed using MRI and magnetic resonance spectroscopy.Fetal liver volume and fetal subcutaneous fat deposition assessed using MRI.In vivo measurements of myometrial contractility on myometrial biopsies obtained at the time of caesarean section.Placental glucocorticoid receptor and 11 βHSD 1 (β hydroxysteroid dehydrogenase 1) and 2 mRNA levels.

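### The first secondary objective is assigned to separate correlations in each arm, which leaves two half-sample estimates per outcome, no combined estimate and no valid test of whether the arms differ (minor)

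*Protocol article*

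**What the plan says.** The first item under Secondary objectives in the protocol article is "To determine the pattern of association between insulin resistance and adverse pregnancy outcomes". It names six outcomes: "pregnancy-induced hypertension, pre-eclampsia, caesarean section, postpartum haemorrhage, maternal weight gain during pregnancy and incidence of the baby's admission to the neonatal unit". Five of these are binary and one, weight gain, is continuous.

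The matching entry under Secondary outcomes is "Maternal insulin resistance at 36 weeks’ gestation, which will be correlated with adverse pregnancy outcomes". It does not mention treatment arm.

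The method is fixed in one sentence under Type of analysis and statistical tests: "Correlations within the metformin and placebo groups will be used to determine associations between insulin resistance and adverse pregnancy outcomes". The article describes no other analysis for this objective.

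**The concern.** The objective and the outcome entry each pose a single question per adverse outcome: is insulin resistance associated with it? The analysis sentence, read plainly, answers that question twice, once among women on metformin and once among women on placebo. Neither estimate uses all the women, and nothing combines them.

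Two problems follow. First, precision is given away, because each estimate rests on half the sample. Second, if one arm shows a significant correlation and the other does not, the pair invites the conclusion that metformin changes the link between insulin resistance and complications. That conclusion would be tempting here, since the article gives the mechanism of any effect as a secondary aim. But a significant result beside a non-significant one does not test a difference.

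**Working it through.** **The plan's own figure.** The article gives no power or error rate for these correlations. Its only calculation is for the primary outcome. With a standardised difference of 0.2/0.6 = 0.333, two-sided 5% and a two-group t test, the required size is 142.2 per group for 80% power and 162.6 for 85%. These round up to the stated 143 and 163, so the plan's figures reproduce.

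**Inputs.**
- Women per arm: 143 (Birthweight centiles, 80% power); 200 (half of the approximate 400 under Design); 224 (half of the 449 randomised, from the Abstract). No loss rate is given, so these serve as a range.
- Level: two-sided 5%. The article states this only for the primary comparison ("at the 5% significance level (2-sided) using a two group t test"); using it here is an assumption.
- True correlation r, equal in both arms: 0.10 to 0.30. This is an assumption, as the documents give no value.

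**Formulas (Fisher z).**
- Power with n women: p = Φ(atanh(r)·√(n−3) − 1.96) + Φ(−atanh(r)·√(n−3) − 1.96).
- Chance that exactly one of two independent arms is significant: 2p(1−p).
- Combined power: the same formula with 2n women. Adjustment for arm costs about one degree of freedom, which is ignored.

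**Example, r = 0.20, 143 per arm.** atanh(0.20) = 0.2027.
- One arm: 0.2027 × √140 = 2.399; 2.399 − 1.96 = 0.439; power 67.0%.
- Both arms combined: 0.2027 × √283 = 3.411; 3.411 − 1.96 = 1.451; power 92.7%.
- Arms differ in significance: 2 × 0.670 × 0.330 = 44.2%.

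| Women per arm | r | Power, one arm | Arms differ in significance | Power, combined |
|---|---|---|---|---|
| 143 | 0.10 | 22.1% | 34.4% | 39.3% |
| 143 | 0.15 | 43.2% | 49.1% | 72.0% |
| 143 | 0.20 | 67.0% | 44.2% | 92.7% |
| 143 | 0.30 | 95.6% | 8.5% | 99.9% |
| 200 | 0.10 | 29.1% | 41.3% | 51.6% |
| 200 | 0.15 | 56.4% | 49.2% | 85.3% |
| 200 | 0.20 | 81.2% | 30.5% | 98.1% |
| 200 | 0.30 | 99.1% | 1.7% | 100.0% |
| 224 | 0.10 | 32.0% | 43.5% | 56.2% |
| 224 | 0.15 | 61.3% | 47.4% | 89.0% |
| 224 | 0.20 | 85.4% | 24.9% | 99.0% |
| 224 | 0.30 | 99.6% | 0.8% | 100.0% |

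**Why two results side by side are not a test.** Suppose, as an illustration, that 143 women per arm give correlations of 0.20 and 0.13. The z values are 0.2027 × √140 = 2.40 (p = 0.016) and 0.1307 × √140 = 1.55 (p = 0.12), so one is significant and one is not. The difference has z = (0.2027 − 0.1307)/√(2/140) = 0.0720/0.1195 = 0.60 (p = 0.55), which is no evidence that the arms differ.

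**Limit of the calculation.** Fisher z applies to a correlation between two roughly normal variables. For the five binary outcomes it is only a rough guide.

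**The case against.** Working within arms has a sound reason. Metformin is expected to change both insulin resistance and the outcomes, so a crude correlation over all women could reflect the treatment effect alone. Correlating within groups prevents that, and reporting the pattern on and off drug suits a trial with a mechanistic aim. This stands against crude pooling. It does not stand against a model adjusted for treatment group, which gives the same protection with the whole sample.

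The phrase could also mean a single pooled within-group correlation, which is close to the fix. If that is intended, the sentence should say so.

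The disagreement figure depends on the unknown r. Since 2p(1−p) peaks at 50% when per-arm power is 50%, values near 50% are the worst case, and disagreement is small once r reaches 0.30. That is correct, and it is why a range is shown.

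A reader might go further and infer a false-positive problem: six outcomes in two arms make 12 tests, so under the null some association would be found in 1 − 0.95^12 = 46% of trials if the tests were independent, or about 37% if the statistics within an arm correlate at 0.5. The documents do not support this as a finding. They state no 5% level for these analyses, introduce the outcomes as an open list, give no correlation between outcomes, and make no confirmatory claim for this objective. Nor does the figure measure the split by arm: six uncorrected combined tests would still give 1 − 0.95^6 = 26% under independence. The absence of a multiplicity rule, an exploratory label or a rule for differing arms is likewise no finding, because a condensed article commonly leaves these to an analysis plan that is not shown.

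**Conclusion.** The point holds as a modest one about efficiency and interpretation. The article positively fixes a method that, read plainly, gives two half-sample estimates for a one-estimate question and no valid basis for saying that the arms differ.

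Assuming a common true correlation of 0.10 to 0.20, a 5% level and 143 to 224 women per arm, the arms would differ in significance in roughly 25% to 50% of trials, and per-arm power would be well below combined power. If the true association is strong, little is lost. The article does not say that significance will be compared across arms, so the misreading is a risk that the method leaves open, not an error that the plan commits. Severity is minor.

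**What to change.** Replace the sentence under Type of analysis and statistical tests with wording such as: *For each adverse pregnancy outcome, the association with insulin resistance at 36 weeks will be estimated in one regression over both groups, adjusted for treatment group (logistic for binary outcomes, linear for weight gain). That coefficient is the result for the objective. Whether the association differs between groups will be judged only from the interaction of insulin resistance with treatment. Within-group estimates will be reported descriptively.*

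This changes wording only; no new data or participants are needed. The downside is that the combined coefficient assumes a common association unless the interaction indicates otherwise, and the interaction is estimated less precisely. On the Fisher z scale at 143 per arm, the standard error of the between-arm difference is √(2/140) = 0.120, against 1/√283 = 0.059 for the combined estimate, so about twice as large. A non-significant interaction should therefore not be reported as proof that the association is the same in both arms.
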